##### Secondary outcomes

Secondary outcomes include changes in FCCH practices from the pre-post surveys and the EPAO and changes in FCCH nutrition and activity environments from the EPAO. This analysis will assess the overall EPAO nutrition score and subscales created by the UNC originators of the tool [102].

##### Exploratory outcomes

Using measured height and weight, changes in children’s BMI and BMI z score and BMI percentile will be calculated for children at all time-points. We will look at both mean values and at-risk categories based on CDC guidelines [103]. Changes in waist circumference will also be assessed and compared to estimates for normal and at-risk categories.

#### Analysis plan

Initially, descriptive statistics will be used to summarize the variable and detect outliers, data entry mistakes and missing values, including exploratory graphical techniques. The normality of the distribution of primary and secondary outcomes, both in their original and transformed state (if necessary), will be examined with a normal probability plot. Demographic and other baseline characteristics will be compared between groups to confirm that the random assignment resulted in statistically similar groups. Any variables found to be different at baseline will be included in adjusted models. Child-level outcomes will adjust for clustering at the FCCH level using GEE models with exchangeable correlation matrices. We will explore the assessment of the intervention’s effectiveness at changing the HEI, physical activity, sedentary behavior variables, and exploratory measures of BMI and BMI z score by experimental group using Analysis of Co-Variance (ANCOVA).

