Once FCCPs complete the entire baseline survey and in-home observation, they are randomized into either the Intervention or Comparison group. FCCPs are randomized in pairs matched based on their primary language spoken and the number of eligible children within the age range of 2–5 years in their FCCH. The data manager randomly assigns all participants to experimental groups using a Microsoft Excel randomization function after which participating providers are notified of their assignment by a phone call from the project coordinator. Evaluation staff members are not made aware of the intervention group assignment during any aspect of data collection preparation or conduct in the field. Participation in the Healthy Start study, and all data collected through observation or other means are stored in a secure, password protected network or in locked file cabinets.

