#### Exploration of group assignment

Demographic and other baseline characteristics will be compared between groups to confirm that the random assignment resulted in statistically similar groups. Any variables found to be different between groups at baseline will be included in final models. Child-level outcomes will be adjusted for clustering at the FCCH level using generalized estimating equation (GEE) models with exchangeable correlation matrices.

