#### Potential mediators and moderators

Potential mediators include FCCP attitudes, beliefs, perceived barriers and self-efficacy measured on the pre-post surveys. Potential moderators include provider age, ethnicity, race, educational level, income level, years in operation as a FCCP, size of FCCH (number of children in care), accept CACFP or not, and hours of training in the past year.

We will explore the mediational hypothesis, which assumes that interventions change mediators, which in turn change outcome behaviors. We will first assess the experimental group variable (Intervention or Comparison) with the primary outcome behaviors. We will then link the experimental group variable with changes in the proposed mediator (e.g., FCCP’s self-efficacy) and will link proposed mediator with the behavioral outcome. We will repeat these steps looking at all potential mediation relationships hypothesized in the intervention logic model. Clearly, the proposed sample size does not provide sufficient power to test simultaneously all these possible mediators without the risk of capitalizing on chance. However, the information gathered from the individual mediational analyses will provide important preliminary data for generating new hypotheses regarding the intervention’s impacts within FCCH and will guide future intervention research.

For moderation, the GEE models described above will be elaborated by including main effects and interactions with experimental condition of putative moderators of the treatment effect, i.e., provider demographic variables. The additional model terms will allow us to test whether these moderating variables were related to changes in outcomes from baseline to 8 or 12 months, and, further, whether these effects differed by treatment.

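### The one stated covariate rule selects variables by chance baseline imbalance rather than prognostic value, which costs precision and leaves the final models unfixed

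*Protocol article*

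**What the plan says.** The rule appears twice in the Protocol article. Under Exploration of group assignment: "Any variables found to be different between groups at baseline will be included in final models". Under Analysis plan: "Any variables found to be different at baseline will be included in adjusted models". Both sections give the baseline comparison the same purpose: "to confirm that the random assignment resulted in statistically similar groups". Neither lists the variables to be compared, and neither says what counts as different.

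The rest of the text bears on this as follows.

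- **Design.** Evaluation overview and randomization procedures: "FCCPs are randomized in pairs matched based on their primary language spoken and the number of eligible children" aged 2 to 5.
- **Clustering.** Analysis plan: "Child-level outcomes will adjust for clustering at the FCCH level using GEE models with exchangeable correlation matrices". No covariates are named.
- **Effect model.** The Analysis plan names ANCOVA for HEI, physical activity, sedentary behaviour and the BMI measures, without saying which covariates it contains.
- **Moderators.** Potential mediators and moderators lists nine provider and home characteristics. Their main effects enter the moderation models; nothing places them in the main effect models.

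**The concern.** Adjustment helps when a covariate predicts the outcome, because it removes residual variance. A between-arm baseline test does not measure that. In a properly randomised trial any difference it finds is chance, so a strong predictor of diet quality or activity is no likelier to be admitted than an irrelevant variable. Three consequences follow.

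1. Precision that the collected baseline data could supply is mostly given up.
2. The covariate list is unknown until baseline data by arm have been inspected. With no threshold and no list of variables, some discretion remains at that point.
3. The matching factors are balanced by design, so they will practically never be found to differ. The rule therefore tends to keep out the variables thought important enough to match on.

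The rule is written to govern the final models, which include those for the primary outcomes.

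**Working it through.** **Inputs from the article.** Final sample of 60 homes per arm, alpha 0.05, power 0.8 or more (Sample size considerations). The article gives no figure for the effect of its covariate rule, so there is none to reproduce. It gives no SD or intraclass correlation either, so the 60 cannot be rederived; it is taken as stated.

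**Assumptions not in the article.** Two-sided tests; baseline differences judged at p < 0.05; a home-level analysis; the number of baseline variables and their prognostic strength as given below.

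**1. Chance that the model changes.** For k independent unmatched variables, P(at least one enters) = 1 − 0.95^k.

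| k | P(at least one) | Expected number (0.05 × k) |
|---|---|---|
| 9 | 37% | 0.45 |
| 15 | 54% | 0.75 |
| 20 | 64% | 1.0 |
| 30 | 79% | 1.5 |

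Any one unmatched variable enters about 5% of the time, however prognostic it is.

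**2. Power with several covariates.** Take 15 independent covariates, three of them prognostic with coefficients 0.4, 0.3 and 0.2. R-squared = 0.16 + 0.09 + 0.04 = 0.29. Total outcome variance is 1 and the true effect 0.515 SD. In closed form, power ≈ Φ(0.515 / √((2/60) × residual variance) − 1.96):

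- no covariates, residual variance 1: Φ(2.82 − 1.96) = 0.81
- the 0.4 covariate only, residual variance 0.84: Φ(3.08 − 1.96) = 0.87
- all three, residual variance 0.71: Φ(3.35 − 1.96) = 0.92

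Simulation of the full two-step rule agrees with this pattern:

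| Model | Power |
|---|---|
| No adjustment | about 80–81% |
| Plan's rule alone | about 80% |
| Plan's rule, with the 0.4 covariate always in (standing for the baseline outcome in ANCOVA) | about 85% |
| Three covariates fixed in advance | about 91% |

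The loss is about 11 points if nothing else is in the model, and about 5 to 6 points if the baseline outcome is.

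**3. Sensitivity to prognostic strength.** Take one unmatched covariate with correlation ρ to the outcome, and an effect of (1.96 + 0.84) × √(2/60) ≈ 0.51 SD.

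| ρ | Power, rule | Power, always in | Type I error, rule |
|---|---|---|---|
| 0.3 | 0.79 | 0.82 | 0.047 |
| 0.5 | 0.81 | 0.89 | 0.044 |
| 0.7 | 0.81 | 0.97 | 0.034 |

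With the covariate always included, type I error stays at about 0.05. In the 15-covariate setting it was about 0.041 to 0.043 under the rule.

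**4. Matching factors.** For a closely matched prognostic factor, the rule admitted it in 0% of simulated trials. If it is left out and pairs are ignored, the standard error is overstated and type I error ≈ 2Φ(−1.96/√(1 − ρ²)). That is 0.040, 0.024 and 0.006 for ρ = 0.3, 0.5 and 0.7; simulation gave 0.041, 0.022 and 0.006. With the factor always included it was 0.047 to 0.051. This is a limiting case of near-exact matching on a strong predictor, and the two larger values of ρ may well be unrealistic here.

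**The case against.** The strongest reply is that the text does not say covariates enter only through this rule. It says that variables which differ will be included and excludes nothing else. ANCOVA needs at least one covariate, and when the question is change in an outcome the natural candidate is its baseline value. This stands in part. A reader might infer that every prognostic variable is left out unless imbalanced; the article does not establish that, and if the baseline outcome is in the model the power loss roughly halves. But the article does not name that covariate, and the rule would still be the only stated route for all others, including the matching factors.

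A reader might also infer more false positives or a biased effect estimate. Neither is supported. The error rate moves below 5%, not above it, and no bias has been shown. The rule works on baseline data alone and does not choose covariates by what they do to the treatment estimate.

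The 37% to 79% range assumes independent variables. The characteristics listed under Demographics and other FCCP and FCCH characteristics are plausibly correlated, and matching on language would tend to balance some of them, so the true chance is probably lower.

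Finally, a condensed article may leave its covariate list to a fuller plan. That would answer a complaint about omission. This point concerns a rule that the article states twice and that a fuller plan would have to override.

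**Conclusion.** The point holds as a defect of a stated rule. Covariates are selected by chance imbalance, the final models are not fixed until baseline data by arm are seen, and the matching factors would almost never qualify. The harm is lost precision and a mildly conservative test.

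The size depends on inputs the article does not give. With 60 homes per arm, three prognostic covariates with total R-squared 0.29 and baseline tests at 0.05, the loss is about 5 to 11 points of power. The lower end applies if ANCOVA already includes the baseline outcome. With a single covariate correlated only 0.3 with the outcome, the loss is about 3 points (0.79 against 0.82). No sample-size figure changes. The change should be made because it is nearly free, not because the trial's conclusions would otherwise be invalid.

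**What to change.** Delete the rule under both Exploration of group assignment and Analysis plan. In its place state that:

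- each outcome model includes, whatever the observed balance, the baseline value of that outcome and the two matching variables (provider primary language and number of eligible children);
- any further prognostic covariates are named before outcome data by arm are seen, for example child age and sex for child-level outcomes (the exact list is the investigators' choice);
- baseline characteristics are reported descriptively by arm and play no part in choosing the model.

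Say explicitly which covariates the ANCOVA contains and that the GEE models use the same set.

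The cost is about two sentences of wording and a few degrees of freedom. Language, child counts and baseline outcomes are already collected, and child age and sex are needed anyway for the planned BMI z scores. No extra participants or visits are required.

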### Outcome evaluation protocols and measures

#### Evaluation overview and randomization procedures

Evaluation measures are conducted with each FCCP at baseline, with the same measures administered when the 8-month intervention is completed and again after 4 months (approximately 12 months after the intervention begins). At baseline, eligible FCCPs complete the first part of the baseline survey on the telephone. Upon completion of this survey, time is scheduled for the project field coordinator to conduct an in-person visit at the FCCH. During this visit, the field coordinator completes the enrollment process, which includes review of the study protocols and expectations, completion of the informed consent and implementation of the second part of the baseline survey. The field coordinator also leaves written consent forms for the parents of the age-eligible children in the FCCH. For a child to participate in the evaluation, parents must give consent for their child to have diet observed by project staff, wear an activity monitor and/or undergo anthropometric measurement. When at least one signed parent consent form is obtained giving permission for at least one of the measures, the two-day observation is scheduled with the FCCH.

The two-day observation by research staff members includes measurement of the physical and social environment of the FCCH as well as children’s dietary intake. During these visits, staff members also conduct anthropometric measures of the eligible children whose parents consented. Consented children also wear accelerometers during the 2 days to measure their activity. Evaluation staff are blinded to group assignment to reduce measurement bias. All measures are described in detail below.

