#### Effect evaluation and analysis

##### Sample size considerations

The proposed final sample size of 60 FCCHs per experimental group with 3 children per site was chosen to detect differences in primary outcomes consistent with changes found in our Healthy Homes, Healthy Families pilot study, as well as effect sizes in [name] and other published research in child care centers [47, 49, 93, 98]. We anticipate that our proposed final sample of 60 FCCHs per condition with power of 0.8 or greater and alpha of .05 will allow for detection of effect sizes of at least 0.25 serving of fruits and vegetables per day and 3 oz of 100% fruit juice or sugary beverage, as well as increase of 2.1% time in moderate/vigorous physical activity or 2.2% screen-time. To account for expected attrition of 10%, we will recruit 66 homes in each experimental group (total *n* = 132).

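### The child-outcome analysis does not bring in the home's mean baseline, although arm is a home-level factor; the possible cost is efficiency, not bias

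*Protocol article*

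**What the plan says.** Under Primary outcomes, the protocol article defines the primary outcomes as changes in children's diet quality and physical activity. Under Exploratory outcomes, BMI measures likewise "will be calculated for children at all time-points".

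Under Analysis plan, child-level outcomes are adjusted for clustering by home using GEE with an exchangeable correlation, and the effect on HEI, activity and sedentary behaviour is assessed "by experimental group using Analysis of Co-Variance (ANCOVA"). The only covariate rule, given there and under Exploration of group assignment, is to add variables that turn out to differ between arms at baseline. The text does not say whether the ANCOVA response is the change or the follow-up value, or at what level the baseline outcome enters.

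Homes are randomised in matched pairs after the baseline survey and two-day observation (Evaluation overview and randomization procedures). The Theoretical framework section has the intervention reach children through the provider and the home. Consent is given by measure: "parents must give consent for their child to have diet observed by project staff, wear an activity monitor and/or undergo anthropometric measurement". The planned analysis set is "60 FCCHs per experimental group with 3 children per site".

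**The concern.** Arm varies only between homes. The precision of the arm effect therefore depends on how well baseline explains differences between home means at follow-up, not differences between children in the same home.

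Consented children in one home eat the same provider's food and share the same play space, usually on the same two observation days. A home's mean may therefore track from baseline to follow-up better than a child's deviation from that mean does. If so, the best between-home slope of follow-up on baseline is steeper than the within-home slope. A model with the child's own baseline alone fits one compromise slope and under-corrects the home means. A plain change score fixes the slope at 1 and, in the settings examined, over-corrects.

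What is at stake is interval width for HEI, MVPA and sedentary time, in a trial where each extra home requires surveys and two-day observations at three time points. A second, smaller matter is that a child with follow-up but no own baseline on a measure drops out of either analysis.

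**Working it through.** **The plan's own figure.** Sample size considerations gives 60 homes per arm with 3 children each, "power of 0.8 or greater and alpha of .05", and for activity an "increase of 2.1% time in moderate/vigorous physical activity or 2.2% screen-time". It states no SD, ICC or baseline-to-follow-up correlation, so the detectable effects cannot be reproduced. They can only be back-solved. Taking a two-sided test, 180 children per arm and design effect 1 + 2·ICC, the standardised detectable difference is (1.960 + 0.842)·√[2(1 + 2·ICC)/180]. This is 0.295 at ICC 0, 0.349 at ICC 0.2 and 0.418 at ICC 0.5. The 2.1-point MVPA effect then implies an SD of 7.1, 6.0 and 5.0 points respectively. Nothing in this fixes the quantities needed below, so those are assumptions.

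**Set-up.** Take unit variance at both times, m = 3 children per home, home-level correlation rH and within-home child-level correlation rC. For a home mean:
- variance V = ICC + (1 − ICC)/m
- baseline/follow-up covariance C = ICC·rH + (1 − ICC)·rC/m
- best between-home slope = C/V

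The variance of the arm contrast is proportional to:
- change score (slope 1): 2V − 2C
- own baseline only, pooled slope b: V − 2bC + b²V
- own baseline plus home mean: V − C²/V

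The pooled b is the generalised-least-squares compromise between C/V and rC, weighted by the inverse residual variances between and within homes and solved by iteration.

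**One setting in full (ICC 0.4, rH 0.7, rC 0.1).** V = 0.4 + 0.6/3 = 0.60. C = 0.28 + 0.02 = 0.30. The best slope is 0.30/0.60 = 0.50 and the pooled slope is 0.254.
- Change score: 1.20 − 0.60 = 0.600
- Own baseline: 0.600 − 0.152 + 0.039 = 0.486
- With home mean: 0.600 − 0.150 = 0.450

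The cut is 1 − 0.450/0.486 = 7.5% against own-baseline ANCOVA and 25% against the change score.

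**Five settings with rH well above rC (3 children per home).**

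| ICC / rH / rC | Pooled slope | Best slope | Cut vs own baseline | Cut vs change score |
|---|---|---|---|---|
| 0.2 / 0.6 / 0.2 | 0.26 | 0.37 | 1.4% | 31.4% |
| 0.4 / 0.6 / 0.2 | 0.30 | 0.47 | 3.4% | 26.7% |
| 0.4 / 0.7 / 0.1 | 0.25 | 0.50 | 7.5% | 25.0% |
| 0.6 / 0.7 / 0.1 | 0.30 | 0.59 | 11.3% | 20.5% |
| 0.6 / 0.8 / 0.2 | 0.43 | 0.69 | 11.8% | 15.5% |

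A GEE simulation with 120 homes and 1 to 5 children per home gave a largest variance ratio of 1.15, a cut of 1 − 1/1.15 = 13%.

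**Settings with the correlations closer.** At ICC 0.3, the cut against own-baseline ANCOVA is 0% for 0.5/0.5, 0.6% for 0.5/0.3 and 2.6% for 0.7/0.3. Over a grid of ICC 0.1-0.5, rH 0.3-0.8 and rC 0.2-0.5 it never exceeds 10.0% (at 0.5/0.8/0.2), where power of 0.80 becomes 0.84. In simulation the empirical SE did not fall in two of three settings (0.108 to 0.109, and 0.115 to 0.116). It fell from 0.118 to 0.111 in the third (0.5/0.8/0.2).

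**Where the gain over a change score comes from.** Moving from change score to own-baseline ANCOVA alone gives cuts of 30.5%, 24.1%, 18.9%, 10.3% and 4.1% in the five settings, in table order. Adjusting for baseline at all is therefore most of the gain at ICC 0.2-0.4 and about half or less at ICC 0.6.

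**Children without their own baseline.** With 15% or 30% of own baselines missing at random and at least one child measured per home, simulated variance ratios were 1.05 and 1.13 even with equal correlations (0.5/0.5, ICC 0.3). These fractions are illustrative. The documents give none, and their 10% attrition refers to homes.

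**The case against.** The strongest reply is that the article does not spell out its model. ANCOVA ordinarily means adjusting for baseline, the exact baseline terms may sit in an analysis plan that is not shown, and the article neither includes nor excludes the home mean. This stands in part. No error can be charged, and the weaker change-score reading is only one the wording permits. What remains is that the article commits to child-level change, GEE and ANCOVA, and its one covariate rule depends on observed imbalance, which would not normally bring in the home mean.

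A reader might infer that the home's baseline information is thrown away. It is not. Under either reading the children's baselines average to the home mean and enter the arm contrast; only the slope may be poor.

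A reader might infer that precision is certainly lost. The documents do not support that. Without an ICC or correlations the loss is conditional, and it vanishes when the two correlations are equal.

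A reader might also infer from consent by measure that children are bound to be lost. Consent withheld for a measure generally removes both baseline and follow-up. Only absence, later consent or turnover leaves follow-up alone, and the article gives no figure for these. Setting a deviation to zero also keeps such a child only if the response is the follow-up value, because a change score cannot be formed. Finally, the shared-meals and shared-space argument concerns diet and activity and does not extend naturally to BMI.

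**Conclusion.** The point holds as an efficiency improvement. Clustering is handled by the GEE and no bias or invalid inference is shown.

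Relative to own-baseline ANCOVA, adding the home mean cuts the variance of the arm effect by 0% to about 12-13%. The upper end needs a home ICC near 0.6 and a home-level correlation several times the child-level one; where the correlations are closer the cut is 0-2.6% at ICC 0.3. Relative to a plain change score, the cut is about 15-31% in the five settings. In the fixed-size settings the slope gain equals about 2 to 16 extra homes (120 × 0.014 to 120 × 0.134).

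All of this rests on assumed ICCs and correlations, equal variances at both times and about 3 children per home. The number of children who would be retained cannot be quantified from the documents.

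**What to change.** For HEI, MVPA and sedentary time, state before analysis that the GEE models the follow-up value, not the change, with arm and two baseline terms: the mean baseline of the home's measured children, and the child's deviation from that mean. For children with complete data, using change as the response with the same two terms would give the same arm estimate, so nothing is lost by this choice.

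Set the deviation to 0 for a child enrolled before randomisation who lacks an own baseline on that measure. Compute the home mean from children measured before randomisation, and do not use this device to admit children recruited afterwards into the primary analysis. State what happens to a home with no baseline at all on a measure, which consent by measure allows. In homes with a single measured child the deviation is simply 0.

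The cost is one extra model term, about one degree of freedom among some 120 homes, and no new data.
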